### Outcomes

#### Primary outcome

The primary outcome will be the live birth rate after the first embryo transfer. Live birth is defined as the birth of a breathing live-born infant with a heartbeat after 28 completed weeks of gestation.

#### Secondary outcomes

Secondary outcomes, including the clinical pregnancy rate, ongoing pregnancy rate, early miscarriage rate, late miscarriage rate, cumulative live birth rate, ectopic pregnancy rate, and time to pregnancy, are listed in Table 1.

**Table 1 Tab1:** Primary and secondary outcome measures of this RCT

Outcome	Measure	Definition
Primary outcome	Live birth	Birth of a breathing live-born infant with a heartbeat after 28 completed weeks of gestation
Secondary outcomes	Clinical pregnancy	Presence of intrauterine gestation sacs at 30–35 days after embryo transfer
	Ongoing pregnancy	Presence of a fetal pole with pulsation at 8–10 weeks of gestation
	Early miscarriage	Miscarriage within 12 weeks of embryo transfer
	Late miscarriage	Miscarriage between 12 and 28 weeks of embryo transfer
	Cumulative live birth rate	Birth of a live-born infant conceived within three embryo transfers. Each time a single embryo is transferred is considered.
	Ectopic pregnancy	Pregnancy outside the uterine cavity
	Time to pregnancy	Time interval between the oocyte retrieval date and clinical pregnancy

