### Interventions

Oocyte retrieval and fertilization (either IVF or ICSI) will be performed according to the standard protocols of each reproductive medical center. For every eligible patient, all embryos will be cocultured in the same medium drop for the first three days after fertilization (Day 0). On Day 4, embryos will be separately washed 3 ~ 5 times to maximally remove potential maternal/paternal DNA contamination derived from polar cells, cumulus cells, and sperm and then cultured individually to Days 5/6. Morphological grading will be performed on Day 5/6 to determine whether a good-quality (superior to grade 4CB) blastocyst has developed according to Gardner’s criteria [19]. After that, the embryos will be vitrified, and the spent blastocyst culture medium will be collected.

For patients in the intervention (niEVT) group, the embryo transfer order will be determined based on the niPGT-A results (primary standard) and morphological grading results (secondary standard). The embryos will be ranked into three groups: Class 1, with a chromosome status of euploid; Class 2, with an undetermined chromosome status (failed genetic testing or noninformative results); and Class 3, with a chromosome status of aneuploid. Embryos of the same group will be further ranked according to their morphological grades (5AA > 5AB > 5BA > 4AA > 4AB > 4BA > 6AA > 6AB > 6BA > 5BB > 4BB > 6BB > 5AC > 5BC > 4AC > 4BC > 6AC > 6BC > 5CA > 5CB > 4CA > 4CB). Embryos in the same group and with the same morphological grade will be randomly selected for transfer. Based on the rules described above, the embryo transfer order can be achieved. A clinical report with the patient information, embryo IDs, and embryo transfer order will be generated and sent to the clinician. Neither the niPGT-A results nor the morphological grading results will be shown on the report.

For patients in the control (conventional IVF) group, the embryo transfer order will be determined based only on the morphological grading results. A similar clinical report in the same format will be generated and sent to the clinician. The morphological grading results will not be shown on the report.

For patients in both groups, the clinicians will perform a single frozen-thawed blastocyst transfer [20] up to three times according to the embryo transfer order of the clinical report. If the prior embryo transfer fails (no conception for any reason), a second/third embryo transfer will be performed.

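### Table 1 times miscarriage from embryo transfer but live birth by gestational age, so the late-miscarriage window extends past the 28-week live-birth threshold

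*Protocol article*

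**What the plan says.** Table 1 of the Protocol article (Methods, Secondary outcomes) defines early miscarriage as "Miscarriage within 12 weeks of embryo transfer" and late miscarriage as "Miscarriage between 12 and 28 weeks of embryo transfer". Both are timed from transfer.

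Two other rows of the table use gestational age. Live birth is "Birth of a breathing live-born infant with a heartbeat after 28 completed weeks of gestation", which agrees with the Primary outcome section: "Live birth is defined as the birth of a breathing live-born infant with a heartbeat after 28 completed weeks of gestation". Ongoing pregnancy is "Presence of a fetal pole with pulsation at 8–10 weeks of gestation".

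Clinical pregnancy is again timed from transfer: "Presence of intrauterine gestation sacs at 30–35 days after embryo transfer".

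Under Interventions, embryos are "cultured individually to Days 5/6", with fertilization as Day 0, and in both arms "the clinicians will perform a single frozen-thawed blastocyst transfer". The article does not say how gestational age is calculated, nor that weeks of embryo transfer means weeks of gestation. Table 1 has no stillbirth row.

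**The concern.** The number 28 closes the late-miscarriage window and opens the live-birth period, so a reader expects the two to meet at one date. They do not, because a blastocyst transfer takes place some time after gestation is conventionally taken to begin. Twenty-eight weeks from transfer is therefore later than 28 weeks of gestation, and there is an interval in which the table allows both a live birth and a late miscarriage.

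What is at stake is the classification of losses in that interval. Early and late miscarriage are separate secondary outcomes, and the Statistical analyses section has each compared between arms after every embryo transfer. Miscarriage also matters to the rationale: the Abstract and Discussion cite fewer miscarriages as a benefit of PGT-A, and the Trial objectives list the miscarriage rate among the effects to be determined. Eight centers supply the data. If one counts from the transfer date and another from gestational age, the same loss can be recorded in two ways.

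**Working it through.** The article prints no day count for this point, so there is no figure of its own to reproduce. The check is date arithmetic.

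**Inputs from the article**
- Early/late cut: 12 weeks after transfer = 12 × 7 = 84 days (Table 1).
- End of the late-miscarriage window: 28 weeks after transfer = 28 × 7 = 196 days (Table 1).
- Live-birth threshold: 28 completed weeks of gestation = 196 days (Primary outcome; Table 1).
- Embryo age: 5 or 6 days from fertilization (Interventions), taken as the age at transfer of the frozen-thawed blastocyst.

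**Assumption, not in the article**
- Gestation is counted from 14 days before fertilization, the usual convention. The alternative, counting from fertilization itself, is shown as a sensitivity check.

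**Formulas**
- Gestational age at transfer, g = offset + embryo age, with offset 14 (usual) or 0 (from fertilization).
- End of the late window in gestational age = 196 + g.
- Overlap past the live-birth threshold = (196 + g) − 196 = g.

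**Results**

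| Convention | Embryo | g (days) | Late window ends at | Overlap |
|---|---|---|---|---|
| Usual | Day 5 | 14 + 5 = 19 (2w5d) | 196 + 19 = 215 d = 30w5d | 19 days |
| Usual | Day 6 | 14 + 6 = 20 (2w6d) | 196 + 20 = 216 d = 30w6d | 20 days |
| From fertilization | Day 5 | 0 + 5 = 5 | 196 + 5 = 201 d = 28w5d | 5 days |
| From fertilization | Day 6 | 0 + 6 = 6 | 196 + 6 = 202 d = 28w6d | 6 days |

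The overlap is above zero in every row. Its size depends on the convention; its existence does not.

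**Reverse check.** For the windows to meet at 28w0d of gestation under the usual convention, late miscarriage would have to end 196 − 19 = 177 days (25w2d) after transfer for Day 5 embryos and 196 − 20 = 176 days (25w1d) for Day 6.

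**Other rows of the table**
- The early/late cut falls at 84 + 19 = 103 days (14w5d) or 84 + 20 = 104 days (14w6d) of gestation. The article sets no other 12-week boundary, so this conflicts with nothing in it.
- Clinical pregnancy at 30 to 35 days after transfer is 7w0d to 7w5d (Day 5) or 7w1d to 7w6d (Day 6). It comes before the ongoing-pregnancy window at 8 to 10 weeks, so the change of clock creates no overlap there.

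**The case against.** The strongest reply is that gestational weeks were plainly meant. The repeated 28 suggests so, and if centers work that way nobody is misclassified. The full protocol is not shown, so the operational rule cannot be seen. This reply limits what can be said about how losses will actually be coded, but it does not rescue the printed text. If gestational weeks were meant, the words about transfer are wrong; if transfer was meant, the windows overlap. The clinical-pregnancy row times its window from transfer in the literal sense, so a literal reading of the miscarriage rows is not far-fetched.

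A reader might also infer more than the article supports:

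- **That every fetal death from 28w0d to about 30w5d becomes a miscarriage.** The row requires a miscarriage first; the weeks only set a window. The article never says that a fetal death after 28 weeks of gestation is a miscarriage. Such a death could be counted as one, no more.
- **That the early/late cut is an error because it falls near 14w5d.** That measures the plan against an outside convention. The cut is defined once and is uniform to within a day across Day 5 and Day 6 embryos. Moving it would shift losses between two categories without changing their sum.
- **That the primary outcome is compromised.** Live birth requires a breathing infant with a heartbeat, so no live birth can be coded as a miscarriage, and a fetal death after 28 weeks is a non-live-birth under either clock. The sample size and the primary test are unaffected.
- **That one arm is favored.** The same definition applies to both arms, and the embryologist, research assistants, clinicians and patients are to be blinded.
- **That the late-miscarriage rate is distorted by a large proportion.** The article gives no miscarriage or stillbirth rate, so no proportion can be calculated.

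**Conclusion.** The inconsistency is real, confined to the 28-week boundary, and minor. As printed, the late-miscarriage window runs 19 to 20 days beyond the live-birth threshold under the usual gestational-age convention, or 5 to 6 days if gestation is counted from fertilization. The choice between these is an assumption, because the article states no convention.

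The consequence is possible misclassification, or inconsistent classification between centers, of fetal losses just after 28 weeks of gestation. It touches the late-miscarriage outcome and any total built from the early and late counts. How many women this involves cannot be computed from the article. This is a fault in definitions printed in full, not detail that an article may leave to a longer document.

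**What to change.** - Put both miscarriage rows of Table 1 on the gestational clock already used for live birth, so that late miscarriage ends before 28 completed weeks of gestation.
- Report fetal death from 28 completed weeks separately, as stillbirth.
- State how gestational age is derived from the transfer date: add 19 days for a Day 5 blastocyst and 20 days for a Day 6 blastocyst.
- Express the 12-week early/late cut on the same clock. This is for consistency, not to repair a contradiction.

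The cost is two edited table rows, one added category and one sentence on the calculation. The article does not list transfer and loss dates as database fields, but the present definitions cannot be applied without them, so no new data should be needed. The clarification should go to all eight centers and be applied without knowledge of allocation.

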### Sample size calculation

The sample size was calculated using an online tool (Sample Size Calculator, https://clincalc.com/stats/ samplesize.aspx) based on the following estimation: an estimated 50% and 60% of patients in the control and intervention groups will achieve live births, respectively. The sample size required is 1036 patients (two-sided alpha: 5%, power: 90% [beta: 10%]). Considering an estimated loss to follow-up rate of 10%, the final sample size will be 1152 patients, with each arm comprising 576 patients.

### Adverse events

Training for adverse event (AE) monitoring will be carried out prior to participant enrollment for the members (including the clinicians, research assistants, and nurses) who will perform the study. AE monitoring will be conducted from the start (after providing informed consent) to the end (19 months after oocyte retrieval) of the trial. Adverse events and serious adverse events (SAEs) are defined as any undesirable medical effects (moderate or serious) occurring for participants with any allocation during the study, regardless of whether they are considered to be related to the intervention or not. All SAEs will be reported immediately to the principal investigator and the Trial Management Committee and subsequently documented in detail in the patient’s medical record and niEVT database. Appropriate medical procedures will be taken until the patients recover or are in a stable condition.

### Data collection and management

The clinical data of 1152 patients will be collected, with 576 patients in each group. Data will be collected and stored in two forms, including paper files and electronic files. All clinical data will be first collected and recorded in paper files, including the signed consent form and all types of medical records. Then, the medical records and the niEVT results will be transformed into electronic files and stored in the central niEVT administration database (an online website developed for data management). For privacy protection, patient identification codes will be assigned to every participant and used to link to the clinical data. All paper files will be stored in the reproductive medical centers for five years, and only the local investigators, clinicians, and research assistants will have access to these files. Only the principal investigator and statistician of this trial will have full access to all the data (except for patient privacy information) of the eight reproductive medical centers.

### Statistical analyses

Clinical data from 1152 patients will be collected for statistical analysis, with 576 patients in each group. The statistical analysis will be performed according to the intention-to-treat (ITT) principle [21, 22] using the latest version of R software (https://www.r-project.org/). On the use of two-sided statistical tests with a significance threshold of 5% in this study. The normality of continuous data will first be examined using a graphical method or the Shapiro–Wilk test. Variables with a normal distribution will be presented as the means and standard deviations (SDs). Differences between groups will be analyzed using Student’s *t test*. Skewed variables will be presented as medians and ranges and analyzed using the Mann‒Whitney U test. Categorical and dichotomous data will be presented as numbers (percentages) and analyzed by the chi-square test. For the primary outcome (the live birth rate after the first embryo transfer) and secondary outcome measures (the pregnancy rate, ongoing pregnancy rate, early miscarriage rate, late miscarriage rate, and ectopic pregnancy rate after every embryo transfer; the cumulative live birth rate of the complete IVF cycle; and the time to pregnancy), differences between the intervention and control groups will be investigated using the Cochran‒Mantel‒Haenszel (CMH) test. Multivariable logistic regression will be used for data transformation when necessary.

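### Between-arm tests at the second and third transfers compare groups selected after randomisation; they are not intention-to-treat comparisons and can mislead in either direction

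*Protocol article*

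**What the plan says.** The Statistical analyses section of the protocol article states that "The statistical analysis will be performed according to the intention-to-treat (ITT) principle". It specifies "two-sided statistical tests with a significance threshold of 5% in this study". For the primary outcome and the listed secondary outcomes, it says that "differences between the intervention and control groups will be investigated using the Cochran‒Mantel‒Haenszel (CMH) test". That list contains "the pregnancy rate, ongoing pregnancy rate, early miscarriage rate, late miscarriage rate, and ectopic pregnancy rate after every embryo transfer". Live birth is treated separately: it is tested after the first transfer (primary) and cumulatively over the cycle (secondary).

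Under Interventions, "the clinicians will perform a single frozen-thawed blastocyst transfer [20] up to three times according to the embryo transfer order of the clinical report". The condition for going on is: "If the prior embryo transfer fails (no conception for any reason), a second/third embryo transfer will be performed". In the niEVT arm, embryos called euploid are ranked first, undetermined ones second and aneuploid ones last, with morphology ordering embryos within each class. The control order uses morphology alone. The article nowhere calls the later-transfer comparisons descriptive, and it sets no denominator of randomised women for them.

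**The concern.** Reaching a second transfer depends on the result of the first, and that result is what niEVT is meant to change. The reordering also means that the embryo left for a second or third transfer differs in kind between arms. A between-arm test at transfer 2 or 3 thus compares two subsets formed after randomisation, so the intention-to-treat label does not describe it.

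At stake is the reading of the secondary results. A p-value for second-transfer pregnancy or miscarriage could point against niEVT, or for it, in a way that reflects which women and embryos were left rather than a treatment effect on the randomised population.

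**Working it through.** **The plan's own figures.** The sample size assumes live birth of 50% (control) and 60% (niEVT), two-sided 5%, 90% power: n per arm = [1.96·√(2·0.55·0.45) + 1.2816·√(0.50·0.50 + 0.60·0.40)]² / 0.10² = 518.04, so 519 per arm or 1038 in total (stated: 1036). With 10% loss, 1036/0.90 gives 1152 after rounding up to two equal arms, which matches. The article gives no figure for later transfers, so the rest is an illustration.

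**Assumed inputs (none is in the article).** 70% of blastocysts are euploid. Test sensitivity and specificity are 85%, and 5% of embryos give no result. Pregnancy is 80% if euploid and 30% or 50% if aneuploid. Live birth is 70% and 3%. Morphology says nothing about ploidy, embryos are independent, and every pregnancy without live birth counts as a miscarriage.

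**Two blastocysts, calculated exactly.** A woman has two euploid embryos with probability 0.49, one of each with 0.42, and two aneuploid with 0.09. In a mixed pair:

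- A euploid embryo is called euploid, undetermined or aneuploid with probability 0.8075, 0.05, 0.1425. For an aneuploid embryo the order is reversed.
- P(euploid ranked strictly first) = 0.8075·0.8575 + 0.05·0.8075 = 0.7328. P(tie) = 2·0.8075·0.1425 + 0.05² = 0.2326. Ties are split evenly, so P(euploid first) = 0.7328 + 0.1163 = 0.849 (control: 0.5).
- The niEVT sequences then have probability: both euploid 0.49; euploid then aneuploid 0.42·0.849 = 0.3566; aneuploid then euploid 0.0634; both aneuploid 0.09.
- First-transfer live birth: control 0.70·0.70 + 0.30·0.03 = 49.9%; niEVT 0.8466·0.70 + 0.1534·0.03 = 59.7%. These are close to the planned 50% and 60%.

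Now take a further transfer only after no conception, with 30% pregnancy if aneuploid:

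- Control: first-transfer pregnancy 0.70·0.80 + 0.30·0.30 = 65.0%, so 35.0% go on. Second-transfer pregnancy is again 65.0%.
- niEVT: first-transfer pregnancy 0.8466·0.80 + 0.1534·0.30 = 72.3%, so 27.7% go on. Second-transfer pregnancy = (0.49·0.2·0.8 + 0.3566·0.2·0.3 + 0.0634·0.7·0.8 + 0.09·0.7·0.3)/0.2767 = 0.1542/0.2767 = 55.7%.

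At 50% pregnancy if aneuploid, the same steps give 71.0% and 65.8%. Second-transfer miscarriage per pregnancy is 23.2% (control) vs 32.8% (niEVT) at 30%, and 29.7% vs 41.8% at 50%. If a further transfer instead follows any failure to reach live birth, these miscarriage differences are 9.3 and 12.8 points. The range is therefore 9-13 points.

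Cumulative live birth with two embryos: under the live-birth rule it is 1 − (1 − 0.499)² = 74.9% in both arms, because order cannot matter when both embryos are used until one succeeds. Under the no-conception rule it is 67.4% vs 70.1% (at 30%) and 64.4% vs 69.2% (at 50%), higher in niEVT.

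**More blastocysts.** Pregnancy per transfer, control vs niEVT, no-conception rule. Control is exact. The niEVT values for 2-5 and 3-6 come from a simulation of one million women with equal mixes of embryo counts. The live-birth rule changes them by about half a point at most.

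| Blastocysts | Pregnancy if aneuploid | 2nd transfer | 3rd transfer |
|---|---|---|---|
| 2 | 30% | 65.0% vs 55.7% | none |
| 2 | 50% | 71.0% vs 65.8% | none |
| 2-5 | 30% | 65.0% vs 66.4% | 65.0% vs 57.5% |
| 2-5 | 50% | 71.0% vs 72.1% | 71.0% vs 67.1% |
| 3-6 | 30% | 65.0% vs 71.6% | 65.0% vs 60.3% |
| 3-6 | 50% | 71.0% vs 75.2% | 71.0% vs 68.9% |

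**Chance of a significant deficit, two blastocysts, 576 per arm.** At 30%: 0.350·576 = 202 vs 0.2767·576 = 159 women; difference 9.3 points; standard error √(0.65·0.35/202 + 0.557·0.443/159) = 5.2 points; z = 1.79; chance about 43%. At 50%: 167 vs 142 women; 5.2 points; standard error 5.3; z = 0.98; chance about 16%.

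**A different denominator does not repair the second-transfer rate.** Over all randomised women, the two-blastocyst case at 30% gives 0.35·0.65 = 22.8% vs 15.4%, partly because fewer niEVT women need a second transfer.

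**The case against.** The strongest reply is that little hangs on these tests. The primary outcome is the first transfer, cumulative live birth is already a listed secondary outcome, and the stopping criteria under Interim analysis do not refer to later-transfer rates. The first-transfer tests within the same phrase are sound. All of this stands, and it limits the point to secondary outcomes.

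A reader might infer more than the documents support:

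- **That the tests will make niEVT look harmful.** The two-blastocyst case does so, but two is only the eligibility minimum and up to three transfers are planned. With more embryos the second-transfer difference vanishes or reverses.
- **That the distortion can be read from live birth.** On the planning rates with two embryos and a 50% second-transfer rate in control, niEVT's second-transfer live birth would be (0.75 − 0.60)/0.40 = 37.5%. But live birth is not on the after-every-transfer list, and this figure assumes another transfer after any failure to reach live birth. The Interventions section explains failure as no conception.
- **That cumulative live birth is equal in the arms while the later tests differ.** That holds in the two-embryo case under the live-birth rule only.
- **That several transfers per woman are pooled as independent records.** The article does not say so. On the planning rates just used, pooling would give 0.75/1.5 = 50% vs 0.75/1.4 = 53.6%, with no apparent harm, although that denominator too is set by earlier results.

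None of these limits restores a randomised comparison at transfers 2 and 3.

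**Conclusion.** The point holds for the second- and third-transfer tests of pregnancy, ongoing pregnancy, early and late miscarriage and ectopic pregnancy. That the groups are selected after randomisation follows from the article's own transfer rule and ranking rule, and needs no assumed figure beyond a test that is informative about ploidy; with an uninformative test there is no distortion.

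Size and direction are not known from the article. Under the stated assumptions, second-transfer pregnancy in niEVT ranges from 5-9 points lower (two blastocysts) through about equal (two to five) to 4-7 points higher (three to six). Third-transfer pregnancy with two to five is about 4-8 points lower. The figures rest on assumed euploidy, test accuracy, pregnancy rates and embryo counts, and show only that the sign can change. The first-transfer tests and cumulative live birth are unaffected if counted over all randomised women. This is worth changing before analysis, but it does not touch the primary conclusion.

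**What to change.** In Statistical analyses, restrict the between-arm tests of these five outcomes to two analyses, each with all randomised women as denominator: (i) the outcome at the first transfer, and (ii) a cumulative per-woman outcome over up to three transfers. Report second- and third-transfer rates by arm as counts and percentages without p-values, and state that these groups are defined by earlier results. Changing only the denominator of the second-transfer rate is not enough, as shown above.

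This is a change of wording and needs no new data. The cost is the p-values for transfers 2 and 3, which have no valid randomised interpretation.

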### Study participants

Eligible subjects must meet all the inclusion criteria. To be enrolled, the following criteria must be met: (1) Couples experiencing infertility who are undergoing their first IVF cycle; (2) Couples undergoing IVF or ICSI as the fertilization protocol; (3) Couples in which the female is aged 20–43 years; (4) Couples in which the female has a body mass index (BMI) of 18–25 kg/m^2^; (5) Couples who agree to the performance of single culture of all embryos on Day 4 (after fertilization); (6) Couples with ≥ 2 good-quality (morphological grade superior to 4 CB) blastocysts on Day 5/6 after fertilization; (7) Couples who agree to undergo single frozen-thawed blastocyst transfer; and (8) Couples in which both partners provide written informed consent.

Subjects who met any of the exclusion criteria will be excluded from the study. The exclusion criteria are as follows: (1) Couples (with any contraindications) who are unable to undergo in vitro fertilization; (2) Couples (with a known chromosomal abnormality) who are eligible for preimplantation genetic testing (PGT) cycles; (3) Couples in which the female has unexplained recurrent miscarriage (≥ 2 times); (4) Couples in which the female has diseases that affect the pregnancy outcome (e.g., untreated hydrosalpinx, untreated intrauterine infection, uterine fibroid diameter > 4 cm, pelvic and abdominal benign tumors > 4 cm, hCG daily endometrial thickness < 7 mm, pituitary tumors and malignant tumors of various tissues and organs); (5) Couples in which the female has a congenital uterine anomaly (e.g., septate uterus, bicornuate uterus, unicornous uterus) or an acquired intrauterine pathology (e.g., adenomyosis, submucosal leiomyomas, intrauterine adhesions); and (6) Couples with severe male factor infertility (e.g., aspermia, azoospermia, cryptozoospermia).

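### Time to pregnancy, a secondary outcome, is assigned the Cochran-Mantel-Haenszel test used for the binary rates, which as written gives no valid comparison of all randomized women

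*Protocol article*

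**What the plan says.** All references are to the protocol article.

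- **Secondary outcomes** makes this a prespecified outcome: "cumulative live birth rate, ectopic pregnancy rate, and time to pregnancy, are listed in Table 1". Table 1 defines it as "Time interval between the oocyte retrieval date and clinical pregnancy".
- **Statistical analyses** lists the primary outcome, the per-transfer rates, the cumulative live birth rate "and the time to pregnancy), differences between the intervention and control groups will be investigated using the" CMH test. The same section commits to intention-to-treat. The other methods it names are the t test, the Mann-Whitney U test, the chi-square test and logistic regression.
- **Interventions** limits single transfers: "up to three times according to the embryo transfer order of the clinical report". **Study participants** asks for at least two good-quality "blastocysts on Day 5/6 after fertilization", so some women may have only two embryos to transfer.
- **Sample size calculation** expects incomplete follow-up: "Considering an estimated loss to follow-up rate of 10%, the final sample size will be 1152 patients".
- **Adverse events** gives the only follow-up limit, for safety monitoring: "to the end (19 months after oocyte retrieval) of the trial".

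**The concern.** The CMH test, listed as it is here beside binary rates, compares categorical tables across strata. Time to pregnancy is a duration. It ends in an event that some women never have and that others may have after they are lost to follow-up. The section describes no event-time strata, categories or scores that would turn the duration into something this test can use.

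An analyst following the text has two options. One is to replace the named method, possibly after seeing data. The other is to analyse only women with a value, meaning those who conceived. Conceiving is a result of treatment, so that comparison is no longer protected by randomization. It also discards the main information, namely that one arm may have fewer women who never conceive. What is at stake is the validity and power of one prespecified secondary comparison.

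**Working it through.** **1. The plan's own figure.** The article gives no figure for time to pregnancy; its only calculation is for the primary outcome, on "an estimated 50% and 60% of patients in the control and intervention groups will achieve live births, respectively". With two-sided alpha 5% and power 90%:

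n per arm = [1.960 × √(2 × 0.55 × 0.45) + 1.2816 × √(0.50 × 0.50 + 0.60 × 0.40)]² / 0.10² = (1.3790 + 0.8971)² / 0.01 ≈ 518.0

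Twice 518 is the stated 1036 (always rounding up gives 519 and 1038). 1036 / 0.90 = 1151.1, hence 1152, or 576 per arm. The figure reproduces, and nothing below changes it.

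**2. Women without a value.** With a constant pregnancy rate p per transfer and k transfers, the share with no time to pregnancy is (1 − p)^k. The article gives no pregnancy rates per transfer, so these are assumptions. Loss to follow-up is ignored here.

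| Assumed rates (control v niEVT) | Transfers | Share without a value | Women of 576 per arm |
|---|---|---|---|
| 50% v 60% | 2 | 25.0% v 16.0% | 144 v 92 |
| 50% v 60% | 3 | 12.5% v 6.4% | 72 v 37 |
| 60% v 70% | 2 | 16.0% v 9.0% | 92 v 52 |
| 60% v 70% | 3 | 6.4% v 2.7% | 37 v 16 |

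The missing values are unequal between arms because they depend on the treatment effect.

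**3. Cost in power.** Simulation of 1000 trials, 576 per arm. Assumptions: 50% v 60% per transfer, 10% loss between transfers, transfers about two months apart.

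| Transfers | Rank test, conceivers only | Log-rank test, all women |
|---|---|---|
| Up to 3 | about 47% | about 98% |
| 1 only | about 5% | about 61% |

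With no difference between arms (three transfers) the rejection rates were 5.1% and 6.2%.

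In the one-transfer row the conceivers-only test sees no effect at all, because the arms differ only in how many conceive. This simulation censors women who do not conceive at their last transfer. That is costly too: for 50% v 60% with 576 per arm, a plain comparison of proportions has power of about 93%, against 61% here. This is a reason to keep such women event-free to a common horizon.

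**4. Direction of the result.** Mean time among conceivers = Σ t·w·p / Σ w·p, where w is the share not yet pregnant. Transfers are assumed at 3, 5.5 and 8 months after retrieval.

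| Rates by transfer, control | Rates by transfer, niEVT | Pregnant | Mean months, conceivers |
|---|---|---|---|
| 50/50/50% | 60/60/60% | 87.5% v 93.6% | 3.875/0.875 = 4.43 v 3.888/0.936 = 4.15 |
| 50/45/40% | 60/40/30% | 83.5% v 83.2% | 3.6175/0.835 = 4.33 v 3.256/0.832 = 3.91 |
| 50/20/10% | 60/50/40% | 64% v 88% | 2.37/0.64 = 3.70 v 3.54/0.88 = 4.02 |

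Only the third row makes the better arm look slower. It needs niEVT to be far better at the second and third transfers. The Interventions section has niEVT change only the order of transfer, with undetermined and aneuploid embryos still in the queue. Moving better embryos forward should, if anything, leave its later transfers no better than control's.

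**The case against.** - **The Mantel-Haenszel family can handle this outcome.** The log-rank test is a Mantel-Haenszel test over event-time strata, and a generalized CMH test with scores can compare ordered values. This stands, so it would be too strong to say that no CMH-type test could serve. But the article describes neither form, and rank scores would still give women who never conceive no value unless a rule assigned one.
- **Censoring rules belong in the full protocol or analysis plan.** This also stands: their absence from an article is no finding. The finding is that the article names a method that does not suit the outcome, and a fuller document would have to override that sentence.
- **Intention-to-treat is stated, and nothing says that only conceivers will be analysed.** Correct. A reader might infer that the plan breaks its own principle. The text supports less: the named test and the definition together offer no analysis that fulfils it, which invites a conceivers-only comparison.
- **A reader might also infer that the result would come out reversed.** That is arithmetically possible, but the required rates fit poorly with an intervention that only reorders embryos.
- **The outcome is secondary.** True, and it limits the weight of the point.

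**Conclusion.** The point holds as a misassigned method for one secondary outcome, and it should be fixed. The wording of the test assignment and the Table 1 definition are enough to establish it; no assumed rate is needed. The primary outcome and the sample size of 1152 do not depend on it.

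Its size does rest on assumptions. For per-transfer rates from 50% v 60% to 60% v 70%, roughly 3% to 13% of women per arm have no value after three transfers and 9% to 25% after two, with more in control. This assumes a constant rate at each transfer and that every woman without a pregnancy uses all the transfers counted. The simulated power loss (about 47% against 98%) also assumes the transfer timing and 10% loss between transfers. The harm shown is selection after randomization and lost power; a wrong direction is not the expected result.

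**What to change.** Remove time to pregnancy from the CMH list and state instead:

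- **Population and time zero:** all randomized women, from oocyte retrieval, the origin in Table 1.
- **Summary:** cumulative incidence of clinical pregnancy by arm.
- **Comparison:** a log-rank test stratified by age and fertilization protocol, the randomization strata. A Cox model or a discrete-time model by transfer, stratified likewise, would serve as well.
- **Women who complete their transfers without pregnancy:** event-free to a common horizon stated in advance.
- **Women lost to follow-up:** censored at last contact.
- **Optional:** the difference in restricted mean time to pregnancy at that horizon, with its 95% confidence interval.

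The horizon should not simply be set at 19 months. That figure comes from adverse-event monitoring. The Abstract plans 24 months of enrolment, while Trial status gives first enrolment on 1 December 2021 and completion in October 2023, some 22 to 23 months later. On those dates only women with retrieval in about the first 3 to 4 months (22 − 19 to 23 − 19) could reach 19 months. The sponsor should reconcile these statements first and then fix the horizon.

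The cost is a short text change and no change in sample size. The definition already requires the dates of retrieval and clinical pregnancy; the sponsor should confirm that last-contact dates are recorded too. The change should be made before data are compared by arm.
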